## Abstract

**Background:**

Early childhood adversity plays an important role in the etiology of borderline personality disorder (BPD). Current evidence suggests that trauma treatment for patients with BPD can be performed safely and that early trauma treatment has a positive effect on the course of PD. However, there is a scarcity of RCTs comparing the effects of the timing of trauma treatment during schema therapy (ST) for BPD on BPD severity. Therefore, the LUCY trial investigates the effects of the timing of trauma treatment by comparing early trauma treatment using imagery rescripting (ImRs) on the course of BPD during ST to trauma treatment in the middle of the treatment course.

**Methods:**

In this multicenter RCT, two conditions are compared among 73 individuals with BPD. The participants receive combined individual and group ST in both conditions. However, in condition (A), participants directly start ImRs in the individual sessions in months 2–4, and in condition (B), participants receive ST-as-Usual (STAU), in which ImRs is not allowed during months 2–4. The treatment follows ST treatment protocols, consists of a fixed combination of individual sessions and group sessions with a maximum of nine patients, and has a maximum duration of 25 months. The primary outcome is change in BPD severity, which is assessed using the Borderline Personality Disorder Severity Index-5 by independent raters blinded to the treatment. Secondary outcome measures include treatment retention, disconnection/rejection schemas, general functioning, posttraumatic stress disorder symptoms, general psychopathological complaints, quality of life, happiness, schemas, and schema modes. Multilevel analysis will be performed to analyze and compare changes in BPD severity between conditions and generalized linear mixed model analyses to test predictors and moderators.

**Discussion:**

This study will increase the knowledge on whether trauma treatment early in therapy positively affects the course of BPD manifestations during ST. When the early application of ImRs leads to a faster decrease in BPD manifestations, the treatment of BPD patients might be shortened, leading to improved treatment outcomes and decreased healthcare expenses. Moreover, the planned sub-studies will expand our knowledge of how ST works and the factors that influence the outcome of treatment.

## Introduction

This article describes the study protocol of the LUCY trial (Legitimizing the Use of Childhood memory rescripting early in the first Year), a multicenter randomized controlled trial (RCT) on the effects of the timing of trauma treatment by imagery rescripting (ImRs) on the course of borderline personality disorder (BPD) manifestations during schema therapy (ST). Among the major evidence-based treatments for BPD, ST has a unique standpoint toward adverse childhood experiences of BPD patients, compared to other evidence-based treatments for BPD [e.g., dialectic behavioral therapy (DBT), mentalization-based treatment (MBT), and transference focused psychotherapy (TFP)], because in comparison with other evidence-based treatments for BPD, traditionally in ST, adverse childhood events are always addressed and processed during ST with ImRs. ImRs is an ST technique that is a highly effective evidence-based stand-alone trauma processing technique for post-traumatic stress disorder (PTSD) and a range of other disorders (1–5). Only more recently, specific trauma-focused DBT and MBT programs have been developed for BPD patients with comorbid PTSD, underscoring the importance of trauma processing in the treatment of patients with PTSD and BPD (6–8). In ST, ImRs is used to process both traumatic experiences that contributed to the development of maladaptive schemas but did not lead to a comorbid PTSD, such as experiences of neglect and emotional abuse, as well as in the case of adverse experiences that (potentially) lead to comorbid PTSD such as abuse and violence experiences (4, 5, 9). Because BPD is related to various types of childhood adversities, it is important to process important experiences that contribute to the maintenance of BPD symptoms during treatment (10).

Trauma processing in the treatment of BPD patients appears important for several reasons. Experiences of early adverse childhood experiences are assumed to play a significant role in the etiology of BPD (11). On average, individuals with BPD have a 13.9 times higher chance of experiencing childhood adversity than non-clinical individuals (12). Compared with other psychiatric groups, BPD patients have a 3.15 times higher chance of experiencing childhood adverse events (13), and they often report a wide range of negative developmental experiences and frequently experience multiple childhood adverse events such as abuse and neglect (10, 12, 14). In addition, adverse events in (early) childhood contribute to the development of early maladaptive schemas (basic mental representations of the self, relationships with others, and the world) and dysfunctional schema modes (encompassing the current emotional, cognitive, and behavioral states of an individual) (15). These schemas have been found to mediate the link between early life experiences and the emergence of personality disorders (16). Finally, the prevalence of PTSD among BPD patients is relatively high, ranging from 34 to 46% (17). This specific group of BPD patients with comorbid PTSD is characterized by a higher level of exposure to traumatic events in interpersonal relationships during both childhood and adulthood compared to BPD patients and PTSD patients (13).

There is evidence that trauma-focused therapy for PTSD can be safely performed in patients with BPD (17). In addition, several studies have investigated the results of combined PD and PTSD treatment on co-occurring personality disorder traits [e.g., (6, 7)]. These studies found a relationship that combined treatment is feasible, acceptable, and safe to administer and may lead to larger improvements in PTSD and BPD than a PD treatment alone. However, little is known about the effects of targeting memories of adverse (childhood) events early in treatment in people with a personality disorder (PD) who do not have comorbid PTSD. A recent RCT by Hafkemeijer et al. (18) compared five sessions of eye movement desensitization and reprocessing (EMDR) therapy (5 weekly sessions of 90 min, 7) to a waiting list control condition (a period of 5 weeks). After 5 weeks of EMDR or 5 weeks of the waiting list control condition, patients in both conditions received ST-as-Usual (STAU) for their PD. After 3 months, significant improvements with medium effect sizes were found for psychological symptoms, psychological distress, and personality functioning in the EMDR condition compared to the STAU condition, indicating that early trauma treatment can be beneficial in the treatment of individuals with PDs (18).

Contrary to these recent positive findings of early trauma treatment, current ST protocols for BPD prescribe trauma treatment in the middle of the treatment course (9). To date, an important reason for postponing trauma processing to the middle phase of ST is the idea that the therapeutic relationship is not yet strong enough, and the patient is not yet ready (9). Trauma processing with ImRs forms an integral and important part of ST for BPD but is usually postponed to the mid-phase of therapy (9), which might be suboptimal given recent positive findings with regard to the effects of early trauma treatment on the course of PD's (18). Trauma processing earlier in therapy might improve the effectiveness of ST, which might lead to shortening the treatment duration and thereby an increase in cost-effectiveness. Therefore, the LUCY trial investigates the effect of early trauma treatment by ImRs on the course of BPD during ST, compared to trauma treatment in the middle of the treatment course.

## This study

Initial evidence suggests that trauma treatment for PTSD can be performed safely in BPD patients, and no stabilization is needed (17). Nevertheless, randomized studies comparing the effects of trauma processing early in ST on BPD severity compared to treatment with no or later trauma processing are lacking. Therefore, this study investigates the effects of early trauma treatment with ImRs on BPD severity during ST.

The central goal of the LUCY trial is to investigate whether ImRs applied early in therapy positively impacts the course of BPD manifestations in ST. In addition, the effects of ImRs on a set of secondary outcomes will be explored, including general functioning, PTSD symptoms, general psychopathology, quality of life, happiness, schemas, and schema modes. A multicenter randomized trial is performed in regular mental healthcare settings. Participants with a primary diagnosis of BPD receive a combination of individual and group ST. Two treatment arms are compared. Both arms start with 1 month of getting acquainted with the ST concepts, forming a working relationship, and formulating a case conceptualization. Thereafter, in condition (A) early ImRs, patients start with ImRs in months 2–4 in their individual sessions, and in condition (B) STAU, patients receive schema therapy as usual (no ImRs allowed during months 2–4). We hypothesize, in accordance with recent findings that show positive effects of early trauma treatment on the course of PD, that recovery from BPD (i.e., reduction of BPD severity) benefits from ImRs applied early in therapy (18).

Second, attrition is quite high in BPD treatment [on average around 40% after one year of treatment in a meta-analysis by Arntz et al. (19)]; if it is indeed the case that patients are not ready for early ImRs, then dropout could be even higher in the early ImRs condition (9). It could however also be the case that providing early trauma processing with ImRs could reduce dropout because trauma-related symptoms, which are associated with high burden and high dropout rates, are treated effectively early. A second objective of this RCT is, therefore, to investigate whether or not trauma processing early in treatment leads to increased dropout from treatment.

Third, the effect of early application of ImRs on the working relationship with the therapist, reported by the patient, is investigated. Early application of ImRs is expected to positively affect the therapeutic relationship in the individual ST compared to usual ST, because in the ImRs, the condition therapist potentially meets the needs of the patients sooner as compared to STAU in which ST techniques can be used that potentially less directly meet the needs of the patient, such as cognitive and behavioral techniques. In ImRs, imagery is used to modify the meaning of traumatic memories by the patient imagining a new script that meets the needs of the patient, thereby directly meeting the unmet need of the patient. It is hypothesized that this could possibly lead to a more secure attachment and improved trust, in other words, a better working alliance. An indication of this comes from a recent qualitative study, in which patients indicated that the therapist being both confrontational (and not avoidant) and able to meet the patient's needs during ImRs was helpful to improve the working alliance (20).

Fourth, the anticipated outcome is that early implementation of ImRs will result in a quicker reduction of the levels of the disconnection and rejection domain schemas, including abandonment/instability, mistrust/abuse, emotional deprivation, defectiveness/shame, and social isolation/alienation, as evaluated by the Young Schema Questionnaire (YSQ), than in usual ST, due to earlier meeting of the needs of the patient.

In summary, multiple explanations are possible for a (possible) positive effect of early ImRs on BPD severity. Therefore, in a sub-study, several mechanisms of change of reduction of BPD severity will be investigated; more specifically, mediation of reduction of BPD severity by schemas, schema modes, working alliance, and PTSD symptoms will be investigated. In addition, in a second sub-study, a qualitative study will be performed in which the experience of therapists and patients with early ImRs will be investigated with semi-structured interviews to gather knowledge on the experiences about the application of early ImRs which will also be used to optimize the application of ImRs early in ST. Finally, the effects of differences in ST dosage (outpatient vs. intensive day clinical treatment—provided by one of the sites, see treatment paragraph for details about the dosage differences) on the effectiveness of ST will be explored.

## Method

### Design

This study design is a multicenter RCT, with two arms (*n* ≥ 73). Both treatments consist of a combination of individual and group sessions. There are two versions of individual ST, to which participants are randomly assigned: (A) experimental ST, in which ImRs is delivered in every individual session during months 2–4 (early ImRs), and (B) STAU, in which patients receive ST-as-Usual, that is, ImRs is not allowed during months 2–4. Therapists in this condition are allowed to use other ST (experiential) techniques, such as chair work and cognitive and behavioral techniques, but are not allowed to use ImRs. After 4 months, therapists are free to use all ST techniques that they think are appropriate and helpful. This study is being carried out in five corporate mental healthcare centers in the Netherlands: GGZ Oost Brabant (locations Helmond and Oss), and PsyQ locations Amsterdam, Rotterdam, and Zaandam. During the study, the PsyQ location in Amsterdam was taken over by the Academic Center for Trauma and Personality (ACTP).

In two PsyQ sites (Amsterdam and Rotterdam), several participants also took part in the Borderline Optimal Treatment Selection (BOOTS) study. The BOOTS study compares the effectiveness of DBT to ST and investigates the optimal treatment selection among individuals with BPD (21). Eighteen participants participated in the BOOTS trial and were randomized to the ST arm. They completed the assessments needed for the BOOTS and the LUCY trial, after which they were randomized to one of the two arms of the LUCY trial.

The study protocol was approved by the ethical committee of the University of Amsterdam (2019-CP-10845). This study is registered at the International Clinical Trial Registry Platform, registration number NL NL7965, first registered on 15 August 2019 and fulfills the World Health Organization Trial Registration Data Set. The procedures adhered to applicable guidelines and regulations. Any changes in the protocol will undergo formal amendments. The ethical committee of the University of Amsterdam will review the amendments, and, upon approval, they will be included in the trial registration.

### Time frame

The trial was registered on 15 August 2019, and the first eligible patient started treatment on 31 October 2019. The last patient started treatment on 24 January 2023 and is expected to complete the treatment on 24 July 24. The last assessment is planned to take place on 24 January 2026, and data collection will be completed after that assessment.

### Patients

Patients were included in the study if they (2) had a primary diagnosis of BPD [assessed with the Structured Clinical Interview for Personality Disorders (SCID-5-PD)] (22), (2) had a score of 20 or above on the Borderline Personality Disorder Severity Index [BPDSI, (23)], (3) were between 18 and 65 years old, and (4) were able to understand, read, write, and speak Dutch (or English for the Amsterdam site, where separate Dutch and English ST is offered). Patients were excluded if they had (1) an alcohol or drug dependency and were in need of a clinical detox (after 3 months of abstinence participation is possible), (2) a comorbid psychotic disorder (when > 1 year in full remission inclusion is possible), (3) an antisocial PD with a history of physical interpersonal violence in the last 2 years, (4) DSM-5 bipolar disorder, type 1 (current or past; if there has been no manic episode in the last year, patients are included) (24), (5) an acute suicide risk, (6) an IQ < 80, (7) received ST of any kind (e.g., individual, group, inpatient, outpatient, and day treatment) in the past year, and (8) were not able to commit to group therapy sessions of 90 min and individual sessions of 45–60 min once a week for 2 years within the treatment period. Patients were asked not to start any other psychological treatment or medicine during screening or during the ST treatment or waitlist period, and prior to beginning ST treatment, medication levels had to remain constant for a minimum of 3 months if not stopped. Non-PD-focused supportive treatment may be continued during the waitlist period and during screening but not during ST treatment in the study and 1-year follow-up period.

### Sample size

At least *N* = 73 participants were planned to be included. Using the approximation proposed by Twisk (25), and assuming an average correlation of 0.5 between measurements [as in (26)], this suffices, given the seven repeated measurements, to reach 80% power to detect a medium effect size of *d* = 0.5 between the treatment conditions. Using the more sophisticated power analysis approach proposed by Moerbeek et al. [(27), p. 191] for multilevel tests of a difference in linear slopes assessed with multiple (i.e., 7) measurements, for a medium effect size (*d* = 0.5) tested at a two-tailed significance level of 0.05, *N* = 39 suffices to reach 80% power. Starting with *N* = 73 and taking into account an early study dropout of 10%, the resulting N=66 suffices to reach > 95% power to detect a medium effect size (*d* = 0.5) and 80% power to detect a small-to-medium effect size of *d* = 0.38. An effect size of *d* = 0.5 between slopes is equivalent to a mean difference between conditions of approximately five points on the BPDSI at the last assessment, which is a relevant difference. Moreover, the sample size of N = 73 suffices to reach more than 80% power to detect at a significance level of 0.05, a difference of 30% in dropout rates during the first year between 20% [which is the approximate dropout rate of ST in individual-group format at 1 year; (26)] and 50%, which would be a substantial and alarming increase in the experimental treatment (25, 28).

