### Statistical analysis

All analyses are planned to be carried out using SPSS or R statistical software. Dimensional outcomes will be analyzed with multilevel analysis using all available data (intent-to-treat principle). Depending on the empirically found distribution of the dependent variable, the appropriate (generalized) linear mixed model will be chosen (e.g., in the case of non-normal distribution, gamma, negative binomial, or Tweedie distributions with a loglink). Time models might be linear, curvilinear, or piecewise, depending on which model fits the data best. The fixed part will contain the main effects of time and treatment arm and their interaction. The random part will contain a covariance structure for the repeated part with the best fit to the data (e.g., AR1, ARMA11, and compound symmetry) and a random intercept for group and/or participant and/or random slopes for time. Adding a random part for each group is important because of the interdependence of assessments of participants per GST group. If necessary, that is in case of substantial differences between treatment arms at baseline, differences at baseline will be controlled for by adding covariates to the model. Multiple imputation methods will be used to handle missing values at the item level. However, completely missing measurements will not be imputed as this is not necessary for multilevel analysis (63). Dropout will be analyzed using survival analysis, with the treatment arm as a factor. If data allow, a multilevel survival analysis will be used to take the dependency of observation by group into account (group as random intercept). The study will use (G)LMM analyses to test predictors and moderators, including working alliances, schema modes, and PTSD symptoms. The analysis will involve adding predictor, predictor x time, predictor x treatment, and predictor x time x treatment interactions to the model.

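### The 80% power quoted for N = 73 is for an average between-arm difference before dropout; it falls to about 76% at the plan's own N = 66 and is not the power of the planned arm-by-time test

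*Protocol article*

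**What the plan says.** The Sample size section gives two calculations for the primary outcome.

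- **Repeated-measures approximation.** "At least *N* = 73 participants were planned to be included". The basis is given as: "Using the approximation proposed by Twisk (25), and assuming an average correlation of 0.5 between measurements". With these inputs the section states that "this suffices, given the seven repeated measurements, to reach 80% power to detect a medium effect size of" d = 0.5 between the arms. No loss to follow-up enters this sentence.
- **Slope calculation.** A second method, for a difference in linear slopes over seven measurements at a two-sided 5% level, needs N = 39 for 80% power at d = 0.5. Dropout enters only here: "taking into account an early study dropout of 10%, the resulting N=66 suffices to reach > 95% power" for d = 0.5, and 80% for d = 0.38. The effect is then translated: d = 0.5 "between slopes is equivalent to a mean difference between conditions of approximately five points on the BPDSI at the last assessment".

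The Statistical analysis section describes the model. "The fixed part will contain the main effects of time and treatment arm and their interaction". "Time models might be linear, curvilinear, or piecewise, depending on which model fits the data best". The residual covariance (AR1, ARMA11 and compound symmetry are the examples given) is also chosen by fit. Table 1 shows the BPDSI at baseline and at 4, 8, 12, 18, 24 and 36 months, so baseline is one of the seven measurements. The article names no averaged post-baseline contrast.

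**The concern.** The sample size and the 80% attached to it appear to come from a formula for the average difference between arms. In the planned model baseline is an outcome measurement, so the treatment effect is carried by the interaction of arm with time. The two tests can differ widely in power for the same effect.

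Two further features of the paragraph add to this. The 10% dropout lowers one calculation and not the other. Both effects are labelled d = 0.5, which invites the reader to take 39 and 73 as two answers to one question, with 73 holding a large reserve. If the interaction turns out null, a reader could cite the 80% as evidence against a medium effect when the test that was run had a different power.

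**Working it through.** **Inputs.** N = 73, 1:1 allocation (Randomization), d = 0.5, correlation 0.5, 10% dropout giving N = 66 (Sample size), visits at 0, 4, 8, 12, 18, 24 and 36 months. The two-sided 5% level is stated for the slope calculation and assumed for the other. Normal approximation, total SD set to 1.

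**1. Reproducing N = 73.** For an average difference over T measurements, n per arm = 2(1.960 + 0.842)² [1 + (T − 1)ρ] / (T d²), where (1.960 + 0.842)² = 7.849 before rounding.

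- T = 7: 2 × 7.849 × 4 / (7 × 0.25) = 35.88 per arm, 71.8 in total.
- T = 6 (follow-ups only): 2 × 7.849 × 3.5 / (6 × 0.25) = 36.63 per arm, 73.3 in total.

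These bracket 73, with nothing added for loss. Power at N = 73 is 80.7% (T = 7) or 79.9% (T = 6), so counting baseline among the seven matters little.

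**2. Same formula at N = 66 (33 per arm).**

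- T = 7: SE = √(2/33 × 4/7) = 0.186; 0.5/0.186 − 1.960 = 0.727; power 76.6%.
- T = 6: SE = √(2/33 × 3.5/6) = 0.188; 0.5/0.188 − 1.960 = 0.699; power 75.8%.

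**3. The arm-by-time test.** Assumed effect: 0 at baseline and 0.5 SD at all six follow-ups. Complete data, no clustering by therapy group.

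Linear time under compound symmetry can be done by hand. The mean visit time is 102/7 = 14.57 months and Sxx = 2420 − 102²/7 = 933.7. The fitted slope difference is 0.5 × (102 − 6 × 14.57)/933.7 = 0.00780 SD per month. Its SE is √(4/73 × 0.5/933.7) = 0.00542. The ratio is 1.44, giving 30% power.

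The other rows come from generalised least squares with a Wald test. The AR1 columns use an adjacent-visit correlation of 0.747, which makes the mean correlation 0.5.

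| Arm-by-time term | CS 0.5, N = 73 / 66 | AR1, N = 73 / 66 |
|---|---|---|
| Linear, 1 df | 30% / 28% | 21% / 20% |
| Quadratic, 2 df | 46% / 42% | 42% / 38% |
| Piecewise, knot at month 4, 2 df | 71% / 66% | 79% / 75% |
| Same model, first segment, 1 df | 72% / 68% | 86% / 82% |
| Piecewise, arms parallel after month 4, 1 df | 79.9% / 75.8% | 87% / 83% |

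Under compound symmetry the last row equals the T = 6 result. The variance of the follow-up mean minus baseline is 0.5 × (1 + 1/6) = 0.583 per person, the same as 3.5/6.

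**4. The slope calculation.** Its figures agree with one another. Scaling from N = 39 at 80% power, the ratio of effect to SE at N = 66 is 2.802 × √(66/39) = 3.645, giving 95.4% for d = 0.5. For d = 0.38 the ratio is 3.645 × 0.38/0.5 = 2.770, giving 79.1%.

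Its effect is a difference that grows to about five points at month 36. If the growth is linear, the mean over the six follow-ups is 5 × 17/36 = 2.4 points, because the mean follow-up time is 102/6 = 17 months. If five points is 0.5 SD (an SD of about 10, which the article does not state), that average is 0.24 SD, less than half of the 0.5 SD average in step 1.

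**The case against.** The strongest reply is that the same section already gives a power for the interaction test. It calls the repeated-measures figure an approximation, then offers a calculation for a difference in linear slopes, with dropout, at above 95%. It nowhere says that the 80% belongs to the interaction. This stands: the planned test is not left without a power figure. But the slope figure covers a linearly growing difference under linear time. It does not give the power for the effect behind N = 73, nor for the curvilinear or piecewise models.

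Second, the constant 0.5 SD effect is not stated in the article, and a step-shaped effect would probably lead a fit-based choice away from a straight line. This also stands. The 30% is the low end under compound symmetry, not a planning figure.

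Third, a reader might infer that none of the permitted time models can reach 80%. The documents do not support that. The piecewise form is left open, holding the arms parallel after month 4 gives 79.9% under compound symmetry at N = 73, and AR1, which the plan names, takes the first-segment test to 86% at N = 73 and 82% at N = 66.

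Fourth, a reader might infer that N = 39 is wrong. If d = 0.5 meant 0.5 raw SD at month 36 with compound symmetry 0.5, linear-slope power would be 73% at N = 73 and 68% at N = 66, and N = 39 would need a within-person correlation of about 0.76 to 0.78. But the slope variance and the standardiser of d are not given, so this shows no error.

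Finally, treating the 10% as wholly lost is cautious, since people who drop out are asked to continue assessments and all available data are used. The N = 66 is nevertheless the plan's own allowance.

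**Conclusion.** The point holds as a matter of what the 80% refers to; it is not a miscalculation, since the figure reproduces.

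- **Dropout.** On the plan's own loss the figure is about 76% (75.8% for six follow-ups, 76.6% for seven measurements). This needs no assumption about the time model. It rests on reading the formula as an average-difference formula, which the reproduction supports but the article does not print, and on a two-sided 5% level.
- **Test.** The 80% does not carry over to the arm-by-time interaction. For an assumed constant 0.5 SD post-baseline effect at N = 73, power runs from about 30% to 79.9% under compound symmetry 0.5 and from about 21% to 87% under AR1 with the same mean correlation, depending on choices left to fit.
- **Effect.** The two values of d = 0.5 need not be the same quantity, so 39 and 73 should not be compared as if they answered one question.

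It does not follow that the trial is underpowered for its interaction test in general. That depends on the shape of the effect and on the covariance, which the article does not fix.

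**What to change.** In the Sample size section:

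1. Restate the repeated-measures figure as the power for the average between-arm BPDSI difference after the stated 10% dropout: about 76% at N = 66.
2. Say that it is not the power of the arm-by-time test.
3. Define the effect behind each d = 0.5 in BPDSI points, with the SD used: an average over follow-up in one case, a difference at month 36 in the other.

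If the N = 73 calculation is meant to apply to the trial's analysis, name the average post-baseline arm difference (months 4 to 36 against baseline), estimated from the same mixed model, as a contrast in the Statistical analysis section.

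The cost is wording and, if chosen, one contrast from a model that will be fitted anyway. The last patient started treatment in January 2023, and nothing here calls for more patients or data. The downside is a stated power about four points less favourable.
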